### Data management and confidentiality

Participant files will be stored in locked cabinets with limited access. Participating centers will only have access to their own center’s data. Data will be entered into SPSS by an independent research assistant. After the trial the principal investigators and the statistician will have access to the data set.

### Statistical analysis

The primary outcome measures of this study are the differences in total and subscale-scores of the ADL and Social-Cognitive subscales of the BOSH and the PBA-s between groups (control versus MT) when baseline differences are taken into account.

Results will be analyzed on an intention-to-treat basis.

A mixed model analysis with repeated measures will be used to analyze the differential effects of music therapy versus recreational activities on the four GOSH and PBA-s scores (week 0, week 8 and week 16, and a follow-up score in week 28). The assessment number, ranging from one to four, will be used as the time variable of the repeated measures.

As stratified randomization often leads to correlation between treatment arms, it is necessary to adjust for the stratification factors in the analysis to obtain correct confidence intervals and p-values. By doing so, we maintain the type I error rate at its nominal level (usually set at 5 %), and avoid a reduction in power [30].

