### Outcome measures

The primary outcome measure, communication skills, will be assessed by the social-cognitive domain of the Behaviour Observation Scale Huntington (BOSH) [26]. The secondary outcome measure, behavior, will be assessed by both the Problem Behaviours Assessment-short version [27, 28] and the third domain (mental rigidity and aggression) of the BOSH (mental rigidity and aggression).

The BOSH contains 32 items in 3 subscales: 1) activities of daily living (ADL) (5 items), 2) social-cognitive functioning (15 items), and 3) mental rigidity and aggression (12 items). Each item is assessed on a 4-point scale. The scores from the first subscale (ADL) range from 1 (self-supporting) to 4 (nursing required). The sum score from the first scale may range from 5 to 20. The scores from the second subscale (social-cognitive functioning) range from 1 (unaffected) to 4 (contact no longer possible); the sum score may range from 15 to 60. Finally, the scores from the third subscale (mental rigidity and aggression) range from 1 (never) to 4 (always); the sum score may range from 12 to 48. Intra- and interrater reliabilities are respectively 0.83 and 0.95 [26].

Assessment of the BOSH will take place within a week before the first intervention (baseline assessment), and will be repeated within a week after the 8th and again within a week after the 16th intervention. 12 weeks after the last intervention, the BOSH will be repeated.

The BOSH takes 15 min and will be administered by nursing staff in charge of the daily care of the patients. Blinding the BOSH-assessors might not be feasible as the nursing staff will have to transport the patients to and from the therapy-rooms. Also in daily life, the chance of the patient divulging his or her allocation towards the nursing staff is big. However, in the process-evaluation following the study all the assessors will be asked whether they were aware of the allocation of the patients.

Since the BOSH is a commonly known assessment scale in the participating HD nursing homes in The Netherlands, no formal training will be carried out prior to the start of the study unless the particular nursing home has no experience with the BOSH.

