Behavioral problems will be assessed with the Problem Behaviours Assessment-short (PBA-s) version [27, 28]. This is a 5-point rating scale, using the scores 0 (absent) to 4 (severe). The PBA-s is a 11-item semi-structured interview and assesses behavioural problems in the 4 weeks prior to the interview. The sum score may range from 0 to 40. In addition, there is a subscale for severity and one for frequency. The PBA-s is a validated and reliable measurement-tool: the interrater reliability is 0.74 for severity and 0.76 for frequency scores (mean kappa), and 0.94 for severity and 0.92 for frequency scores (weighted kappa) [29]. The respondents of this face to face semi-structured interview are the patient and a knowledgeable informant (spouse or caregiver) together.

Assessment of the PBA-s will take place following the same time-schedule as the BOSH-assessments. The PBA-s will be scored by independent, formerly trained assessors who will be blinded to group allocation of the patients. After the last assessment, the assessor will be asked whether or not he inadvertently found out about the patient’s allocation in order to verify the success of the blinding. Where possible, subjects are interviewed in the presence of a knowledgeable informant (primary caregiver).

After consulting a member of the PBA-workgroup we decided to adjust the 4-week retrospective view of the PBA-s to 1 week, due to the short time-frame in which it is administered (every 8 weeks).

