### Sample size

The minimal clinically important change or difference (MCIC/MCID) in the scale serves as important input for the sample size calculations. Unfortunately, data about these scale-characteristics are unavailable. We anticipate that the population in the present study will differ little from the population previously used in the study by Timman et al. [26] from which we derived data on means and standard deviations for the subscales of the BOSH. If we assume that the values in the control group will change little over the course of the study, whereas those in the experimental group will improve by 25 %, and if we further assume an α of 0.05 and a β of 0.20, then the following sample size would be required:ADL: original mean ± SD = 2.25 ± 0.88; improvement of 25 % will result in a mean of 1.69 and if we conservatively estimate a reduction in SD to 0.75, we would require an N of 30 per group for the ADL subscale (for an effect size of 0.55 (moderate));Social-Cognitive: original mean ± SD = 2.10 ± 0.79; improvement of 25 % will result in a mean of 1.58 and if we conservatively estimate a reduction in SD to 0.75, we would also require an N of 30 per group for this subscale (for an effect size of 0.52 (moderate)).

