## Discussion

Music therapy is a promising non-pharmacological intervention. Through stimulation of the expressive and communicative skills, it is hypothesized that this therapy will result in improving activities of daily life and social-cognitive functioning as well as reducing behavioral problems, thus leading to an improvement in the quality of life.

In general, music therapy can be offered either individually or in group sessions, with other patients or with family members. The sessions can be “tailor-made” for the patient and his needs.

In this study, patients in both the intervention- and the control group will participate in group interventions with three to five participants. The decision to choose group-interventions rather than individual interventions is based on the assumption that the interaction between group-members will stimulate communication [31]. In this article, Magee concludes that music therapy is recommended in the middle and the advanced stages of HD. Group sessions allow the patient the time needed for delayed responses, allowing natural “time out” from responses which require attention or concentration. The number of participants in each group has to be determined carefully. In a systematic literature review, Ing-Randolph et al. [32] suggest that group size matters with music interventions addressing certain stages of dementia-associated anxiety. Although Yalom [33] states that a group consisting of fewer than five members results in a decrease in member interaction, this is not the case when working with HD-patients where smaller groups are preferable [31].

Based on earlier RCTs and a meta-analysis of the dose-effect relationship of music therapy in different settings and populations, we expect a treatment duration of 16 weekly sessions, each session lasting 60 min, to be sufficient for detectable developments [13, 14].

The decision to apply the BOSH as the primary outcome measures instead of a QoL-scale requires some clarification; in our opinion, no validated QoL-scale (generic nor disease-specific) is sufficiently sensitive to be used in the very late stage of the disease.

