The BOSH was developed to provide an observational instrument for monitoring the behavioural aspects of the patient in later stages. Expressive and communicative skills are specifically measured within the social-cognitive functioning-subscale. In combination with its 2 other subscales (ADL and mental rigidity), we believe that the scale is so broad that it covers most of the QoL-domains. In the present study, we are planning to analyze the total score of the BOSH.

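### The outcome section names one primary outcome and the analysis section names three or four; with no decision rule, the result that decides the trial is undefined

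*Protocol article*

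**What the plan says.** Four places in the protocol bear on which outcome is primary.

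- **Methods, Outcome measures.** One primary outcome: "The primary outcome measure, communication skills, will be assessed by the social-cognitive domain of the Behaviour Observation Scale Huntington (BOSH"). The PBA-s is placed lower: "The secondary outcome measure, behavior, will be assessed by both the Problem Behaviours Assessment-short version", together with the third BOSH domain (rigidity and aggression). The ADL domain is described but given neither status.
- **Methods, Statistical analysis.** The primary outcome measures, in the plural, are the "differences in total and subscale-scores of the ADL and Social-Cognitive subscales of the BOSH and the PBA-s", compared between groups with baseline taken into account.
- **Methods, Sample size.** The calculation says "assume an α of 0.05 and a β of 0.20" and gives 30 per group for ADL and 30 per group for social-cognitive, with no division of alpha. It does not state whether the test is one- or two-sided.
- **Discussion.** It refers to "The decision to apply the BOSH as the primary outcome measures instead of a QoL-scale" and adds that "we are planning to analyze the total score of the BOSH".

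The only statement about type I error, in Statistical analysis, concerns adjustment for the stratification factors. It does not deal with several primary scores.

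**The concern.** The two Methods sections cannot both hold. The PBA-s is secondary in one and primary in the other. ADL is primary in the second and has no rank in the first. Because the contradiction stands in the published text, it is not a detail left to an analysis plan: a later plan could choose either list and cite the protocol for it.

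What is at stake is the meaning of a positive result in a trial of 60 patients. A difference on ADL or the PBA-s alone could be reported as meeting a stated primary outcome even if the social-cognitive domain, which carries the trial's communication hypothesis, showed nothing. Without a rule fixed before the data are seen, the chance of a false claim depends on how the list is read afterwards.

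**Working it through.** **1. The plan's own figure.** Inputs from Sample size: ADL mean 2.25 falling to 1.69 (difference 0.56); social-cognitive 2.10 falling to 1.58 (difference 0.52); reduced SD 0.75; alpha 0.05; power 80%; 1:1 allocation. The formula is n per group = 2(z_α + z_β)²(SD/difference)².

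- Two-sided, (1.960 + 0.842)² = 7.85. ADL: 2 × 7.85 × (0.75/0.56)² = 28.2, so 29. Social-cognitive: 2 × 7.85 × (0.75/0.52)² = 32.7, so 33 (34 by t-test).
- One-sided, the stated 30 is matched within two patients for both subscales: 28 and 28 by t-test with the original and reduced SDs pooled, or 31 and 29 by the normal approximation with the original SDs.
- Two-sided t-test power at 30 per group with SD 0.75 is 81% for ADL and 75% for social-cognitive.

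So 30 per group is reproduced for ADL two-sided, and for both subscales only one-sided. Each subscale uses the whole 0.05.

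**2. How many primary scores.** The sentence in Statistical analysis gives three at the least: ADL, social-cognitive and PBA-s. Its word for a total most naturally means the BOSH total, which the Discussion plans to analyse; that makes four.

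**3. False-positive rate if any one score suffices.** Each score is tested at two-sided 5% with no true effect. The documents give no correlations between scores, so these are assumed and shown as a range.

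*Three scores.* Independent: 1 − 0.95³ = 14.3%. Equally correlated (simulated normal test statistics):

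| Correlation | Rate |
|---|---|
| 0.3 | 13.6% |
| 0.5 | 12.6% |
| 0.7 | 10.9% |
| 0.9 | 8.4% |

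*Four scores.* Independence gives 1 − 0.95⁴ = 18.5%, but it cannot hold when one score is the BOSH total, because 5 + 15 = 20 of its 32 items are the ADL and social-cognitive items. The total was therefore simulated as the sum of its subscales. Per-item SDs were 0.88 for ADL (5 items) and 0.79 for social-cognitive (15 items), from Sample size, and an assumed 0.7 for rigidity/aggression (12 items). The same correlation was assumed among the three subscales and the PBA-s:

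| Correlation | Rate |
|---|---|
| 0 | 16.7% |
| 0.3 | 15.2% |
| 0.5 | about 13.5% |
| 0.7 | 11.5% |

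Changing the assumed rigidity/aggression SD to 0.6 or 0.8 per item leaves the range at about 11–17%.

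**4. If all scores had to succeed.** The joint false-positive rate cannot exceed that of any single test, 5%. Joint power cannot exceed the lowest single power, which is at most 75% two-sided, since that is the figure for social-cognitive alone.

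**The case against.** Several stronger readings are tempting, and the defence against them is sound.

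- **That there are at least four primary scores.** The sentence is ambiguous: its total could be the PBA-s total or each subscale's sum score, and the Discussion does not call the BOSH total primary. Four is the natural reading; three is the minimum.
- **That there are six, counting PBA-s severity and frequency.** Outcome measures mentions these ("In addition, there is a subscale for severity and one for frequency"), but nothing clearly makes them primary. The independent-score figure for six, 1 − 0.95⁶ = 26.5%, also assumes away the overlap between scores.
- **That the error rate is above 5% as a matter of fact.** This needs a rule that any one score suffices, and none is stated. That each score would be tested at 5% is itself inferred from the sample-size alpha and the nominal level mentioned for stratification.
- **That the sample-size section makes ADL primary.** It never uses the word, and sizing for a second subscale does not by itself change its rank.
- **That rigidity/aggression has been dropped.** Its absence from a list of primary outcomes agrees with its secondary status.
- **That the analysis section's mention of four scores confirms four endpoints.** There it refers to the four assessments.

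What remains is the contradiction between Outcome measures and Statistical analysis. Nothing elsewhere reconciles them.

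**Conclusion.** The point stands as a contradiction about which result decides the trial, with no hierarchy, alpha split or any/all rule to resolve it. The inflation is conditional: about 8–14% for three scores or 11–17% for four if any one suffices, and no more than 5%, at a cost in power, if all must succeed. The ranges rest on assumed correlations (0 to 0.9 for three scores, 0 to 0.7 for four) and, for four, on the assumed rigidity/aggression SD. The contradiction itself needs no assumption and should be removed before any outcome data are seen.

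**What to change.** Replace the first sentence of Statistical analysis so that the BOSH social-cognitive subscale, as in Outcome measures, is the sole primary outcome. Name one deciding time point or contrast (for example week 16, the end of intervention), tested at 5%. Otherwise weeks 8, 16 and 28 would still leave several candidate tests. List ADL, rigidity/aggression, BOSH total and PBA-s as secondary, either Holm-adjusted or labelled supportive, and align the Discussion wording.

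Base the sample-size statement on social-cognitive only, state sidedness, and restate power: about 75% at 30 per group if two-sided with difference 0.52 and SD 0.75, where 34 per group would give 80%.

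The cost is a change of wording, a power statement that may be slightly less favourable, and giving up a claim of success on ADL, BOSH total or PBA-s alone. Keeping four primary scores would cost more. With Bonferroni at 0.05/4 = 0.0125 (two-sided, SD 0.75, normal approximation), ADL needs 41 and social-cognitive 47 per group; at 30 per group power is about 65% and 57%.

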### Randomisation

In order to minimize the impact of any between-center differences on the trial results, the participating centers will be stratified in the randomization process. Participants will be randomly assigned to either control or experimental group with a 1:1 allocation. To generate the random allocation sequence we use the method of center-stratified, block-permuted randomization [24]. The block size will vary. To diminish the chance of predictability, the date of signing the informed consent will determine the sequence in which the patients will be randomized. Not until all baseline measurements have been completed, the randomization code will be released to ensure allocation concealment.

Randomization will be conducted without any influence of the principal investigators, raters or therapists.

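### The mixed model treats week 0 as an outcome with neither a baseline covariate nor a common week-0 mean; fitted in the usual way, it gives a change-from-baseline contrast that is less precise than baseline adjustment

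*Protocol article*

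**What the plan says.** The Statistical analysis section of the protocol article defines the main comparison as the difference in scores "between groups (control versus MT) when baseline differences are taken into account". The model that follows is a repeated-measures mixed model for the four "GOSH and PBA-s scores (week 0, week 8 and week 16, and a follow-up score in week 28") (the first acronym is evidently the BOSH). On time it says: "The assessment number, ranging from one to four, will be used as the time variable of the repeated measures". Assessment one is therefore week 0, and week 0 is modelled as an outcome.

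The only adjustment the section names is for the stratification factors, made partly to protect power. It does not list the week-0 score as a covariate, and it does not say that the arms share a week-0 mean.

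Two other places bear on this. The Randomisation section says: "Not until all baseline measurements have been completed, the randomization code will be released to ensure allocation concealment". The Sample size section works from means and SDs alone, with no correlation between baseline and follow-up, and concludes for the social-cognitive subscale that "we would also require an N of 30 per group for this subscale".

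**The concern.** If each arm has its own mean at each of the four assessments, the group effect at week 8, 16 or 28 can be corrected for baseline only by subtracting the group difference at week 0. With complete data that is the difference in mean change. It subtracts baseline with a fixed coefficient of 1, whereas covariate adjustment uses the regression coefficient. The variance is larger whenever the correlation ρ between week 0 and the later visit is below 1.

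Estimating a separate week-0 mean per arm also buys nothing. Allocation is released only after baseline is complete, so the expected week-0 means are equal by design.

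At stake is the width of the confidence interval, and hence the power, for the social-cognitive comparison with 30 patients per arm. The same applies to every other BOSH or PBA-s score put through this model.

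**Working it through.** **Inputs from the Sample size section**
- Error rates: "if we further assume an α of 0.05 and a β of 0.20". Sidedness is not stated.
- Starting values: "Social-Cognitive: original mean ± SD = 2.10 ± 0.79".
- Target for the music therapy arm: a mean of 1.58 after the assumed 25% gain, with the SD taken as 0.75.
- 30 per arm, 1:1 allocation.

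**Assumptions of this check**
- Two-sided 5% test, with one-sided results shown for comparison.
- ρ between week 0 and the tested visit, which the article does not give, varied from 0.4 to 0.83.
- One common SD, complete data, no allowance for clustering by therapy group.

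**The plan's own figure.** The difference is 2.10 − 1.58 = 0.52. With n = 2(z₁₋α + z₁₋β)²SD²/0.52² per arm:
- One-sided, SD 0.79: 2 × (1.645 + 0.842)² × 0.79²/0.52² = 28.5, so 29.
- Two-sided: 33 (SD 0.75), 35 (pooled SD) or 37 (SD 0.79).

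So 30 is close to the one-sided result and somewhat low for a two-sided test. None of these calculations uses baseline.

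**Variance of the group effect at one visit**, per arm and in units of SD²:
- Follow-up score alone: 1
- Change from baseline: 2(1 − ρ)
- Adjusted for baseline: 1 − ρ²

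The ratio of change to adjusted is 2(1 − ρ)/[(1 − ρ)(1 + ρ)] = 2/(1 + ρ).

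Generalised least squares on a four-visit model with 30 per arm and a compound-symmetric correlation agrees. At ρ = 0.7 the week-16 effect has variance 0.0400 (SD = 1) with free week-0 means. It is 0.0340 with a common week-0 mean, which is exactly the baseline-adjusted value (2/30)(1 − 0.49). Having week 0 in the response therefore costs nothing by itself; the loss comes from leaving the two week-0 means free.

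**Power.** Difference 0.25 × 2.10 = 0.525; pooled SD √[(0.79² + 0.75²)/2] = 0.770; standardised difference 0.525/0.770 = 0.68. This is divided by √[2(1 − ρ)] or √(1 − ρ²) and put through the noncentral t distribution with 30 per arm.

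| ρ | Variance ratio, change/adjusted | Two-sided power, change | Two-sided power, adjusted | One-sided power, change | One-sided power, adjusted |
|---|---|---|---|---|---|
| 0.4 | 1.43 | 65.9% | 80.8% | 76.9% | 88.5% |
| 0.5 | 1.33 | 73.8% | 85.0% | 83.2% | 91.4% |
| 0.6 | 1.25 | 82.7% | 90.0% | 89.8% | 94.7% |
| 0.7 | 1.18 | 91.8% | 95.3% | 95.8% | 97.8% |
| 0.8 | 1.11 | 98.4% | 99.1% | 99.3% | 99.7% |
| 0.83 | 1.09 | 99.4% | 99.6% | 99.8% | 99.9% |

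At ρ = 0.5 the standard errors are 0.770 × √(2/30 × 1.00) = 0.199 for change and 0.770 × √(2/30 × 0.75) = 0.172 adjusted.

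For comparison, the follow-up score alone gives 73.8% two-sided. The change contrast is worse than ignoring baseline below ρ = 0.5 and better above it.

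**The case against.** **The model terms are not given.** The article states neither the fixed effects, nor the tested contrast, nor whether the week-0 means are free. A model with a common week-0 mean also fits the text and loses nothing. A reader might infer that the plan commits to a change-score analysis, or that modelling week 0 as an outcome is itself the error; the documents support neither. What remains is narrower. A common mean needs an explicit constraint. The section puts week 0 in the response, specifies its adjustment and names only the stratification factors, so the default fit is the less precise one.

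**Validity is untouched.** A reader might infer bias, because a chance baseline imbalance shifts the change estimate by (1 − ρ) times that imbalance. An imbalance of one standard error, 0.770 × √(2/30) = 0.199, shifts it by 0.099 at ρ = 0.5, or 19% of 0.525. But such shifts average to zero over randomisations. They are the same loss of precision seen conditionally, and not a second fault.

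**The size is not documented.** The BOSH reliabilities in the Outcome measures section (0.83 intra-rater, 0.95 inter-rater) are not correlations over 16 or 28 weeks. If ρ is nevertheless that high, the power gain is negligible. The disease is progressive and the TFC limit was set to make the group homogeneous, so a lower ρ is plausible, but it is not established. One-sided, the gain at ρ = 0.5 is about 8 points, not 11. These limits stand.

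**The sample size is not overturned.** It rests on an unadjusted comparison, and above ρ = 0.5 the change contrast has more power than that.

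**Conclusion.** The point holds as one of efficiency. As written, the model fitted in the usual way gives a difference in change from baseline, with 2/(1 + ρ) times the variance of the baseline-adjusted estimate.

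On the two-sided assumption, at ρ of 0.4 to 0.5 the change contrast falls short of the intended 80% power while the adjusted analysis reaches it. The gain is about 7 points at ρ = 0.6 and 3.5 points at 0.7, and it is under 1 point at 0.8 or above. One-sided gains are smaller throughout. For any ρ below 1 the direction does not reverse, apart from the few degrees of freedom spent.

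The conclusion rests on free week-0 means, which is an inference from the text, and on a ρ and a sidedness that the article does not give. It implies neither bias nor an inflated type I error. The change is worth making because the baseline score is already collected and the remedy costs almost nothing.

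**What to change.** In the Statistical analysis section, specify one of two equally precise models:

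1. Take the scores at weeks 8, 16 and 28 as the response. Include treatment, assessment as a categorical factor, treatment-by-assessment, centre, and the patient's own week-0 score on the same scale with its interaction with assessment.
2. Keep all four scores in the response with the same categorical terms and centre, but constrain both arms to a common week-0 mean. This version also keeps patients who have only a baseline score in the intention-to-treat analysis.

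In either case, report the adjusted group difference at each visit in place of the difference in change. The cost is one or two sentences before unblinding and a few model degrees of freedom, with no new data, patients or staff.
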